## Discussion

The aim of this mixed-method single-blind randomized controlled trial is to examine the efficacy of the Functional Cognitive and Sensory Treatment (F-CaST), an innovative personalized therapy in men with SUD residing in a TC. We expect that the F-CaST will lead to improved everyday performance and longer length of stay in the TC, compared to the control group. If the F-CaST will show to be effective, cognitive and sensory strategies may be incorporated as an adjunctive intervention in SUD rehabilitation and will support the need to provide intervention programs based on occupational performance to SUD population. Moreover, we believe that the effectiveness of the intervention program will be found at each of the assessments, thus strengthening the effectiveness of the intervention program over time.

The following study limitations will need to be taken into account. The fact that only men with SUD will be recruited from a single TC, will limit the generalizability of the findings to women. Future studies utilizing the F-CaST should definitely include women preferably from therapeutic communities. F-CaST group will be compared to a control group, who will receive standard care, and not an active control group. The duration of the intervention is short and therefore we might not be able to demonstrate effectiveness.

We envision that F-CaST, which is a novel intervention, will show to improve rehabilitation outcomes of men with SUD. F-CaST will fill gaps in current rehabilitation and expand our.

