**Fig. 1 Fig1:**
[figure not shown]
Mixed-methods approach; see the Quantitative and Qualitative outcome measures. This should appear below the Figure: T1- pre-intervention; T2- post-intervention; and T4- 3-month follow-up; COPM- Canadian Occupational Performance Measure; TC- Therapeutic Community; CTT- Color Trails Test; BRIEF-A- Behavior Rating Inventory of Executive Function-Adult Version; SRQ-IS-The Sensory Responsiveness Questionnaire-Intensity Scale; SE-Self Efficacy; NGSE- The New General Self-Efficacy Scale; SRSI- The Self-Regulation Skills Interview

Assessments will be conducted at four time points: T1 pre-intervention; T2 post-intervention; T3 one-month follow-up; and at T4 3-month follow-up, by assessors blinded to group allocation (See Fig. 2). Assessors are licensed occupational therapists, who are trained to administer and score all of the assessments. This study design will allow to identify changes in performance due to the intervention and verify whether the changes are stable. Since high dropout rates have been reported, repeated follow-up assessments are important. In addition, a qualitative investigation including in-depth interviews with the participants will be conducted to provide a deeper understanding of their perceived deficits and how these impact their everyday performance and treatment compliance in the TC (See Fig. 1).

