### Sample size

The sample size was calculated to (i) detect a minimally clinically important difference of the primary outcome measure of everyday (occupational) performance (COPM; see below) with 80% power and a significance level of 0.05, and (ii) to account for a 40% dropout. Thus 24 participants per group will be recruited providing a total of 48 participants for the study**.**

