## Data analysis

Descriptive statistics will be used to describe the participants in each group, in terms of their, demographic information and SUD parameters, primary and secondary outcome measures. Pre-intervention differences between the two groups will be analyzed using t-Test for independent samples (continuous measures) or Chi square (dichotomous measures). A repeated measures ((2)X4) analysis of variance ANOVA will be used to compare within- and between- group scores, for time (T1, T2, T3, T4) comparing the F-CaST to standard care and for interaction time*group effect.

To assess the clinical meaningfulness of the outcomes, the Partial Eta squared in ANOVA effect size will be calculated. Partial Eta squared is interpreted as the proportion of the total variability in the dependent variable that is accounted for by variation in the independent variable. ANOVA Partial Eta squared of 0.01, 0.06 and 0.14 are considered small, medium and large effect sizes (respectively).

Statistical significance will be set at p < 0.05, and all analyses will be conducted using SPSS for Windows version 27.0 (SPSS Inc, Chicago, IL). The transcripts of each of the four in-depth interviews will be analyzed using content analysis (an initial review, the development of mapping categories, and the building of a mapping categories tree) [77].

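### The named ANOVA tests do not by themselves show an F-CaST effect at T2, T3 and T4, although the article expects an effect at each assessment and stable change

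*Protocol article*

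**What the plan says.** Four assessments are planned: "T1 pre-intervention; T2 post-intervention; T3 one-month follow-up; and at T4 3-month follow-up". The Methods text beside Fig. 1 gives the purpose of the repeated visits: to identify change due to the intervention and to "verify whether the changes are stable". The Discussion adds the expectation that "we believe that the effectiveness of the intervention program will be found at each of the assessments", and presents this as strengthening the evidence over time.

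The Data analysis section names a two-group, four-time repeated measures ANOVA "to compare within- and between- group scores, for time (T1, T2, T3, T4) comparing the F-CaST to standard care and for interaction time*group effect". The threshold is general: "Statistical significance will be set at p < 0.05". The article names no between-arm comparison at an individual visit. It also states no rule for turning a significant ANOVA term into a statement about a particular visit.

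The Sample size section aims to "detect a minimally clinically important difference of the primary outcome measure", the COPM, "with 80% power and a significance level of 0.05, and (ii) to account for a 40% dropout", and arrives at 24 per arm. It gives no value for the clinically important difference and no standard deviation.

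**The concern.** The article says what it wants to learn from T3 and T4, namely whether the benefit persists. The tests it names answer different questions. The time-by-group test asks whether the arm difference is constant over the four visits, and an effect that appears at T2 and then disappears violates constancy as much as one that appears at T2 and stays. The group effect asks whether the arms differ on average over four visits, one of which precedes randomisation.

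If these two tests were the only basis for the conclusion, a significant result could be reported alongside the durability expectation without having tested it. Persistence is the reason for collecting T3 and T4, so the analysis should contain a quantity that measures it.

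**Working it through.** **Inputs.** From the Sample size section: 24 per arm, 40% dropout, 80% power, level 0.05. From the Data analysis section: two groups, four times. Assumed, because the article gives no values: the standardised effect d, the correlation rho between visits, equal variances, compound symmetry, two-sided testing, and analysis of completers only.

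**The plan's own figure.** Completers per arm are 24 × 0.6 = 14.4. By the usual two-mean formula, a difference of about 1.06 SD needs 14 per arm, and 14 / 0.6 = 23.3, rounded up to 24. So 24 is consistent with a difference of about that size. This is not a true reproduction, since the clinically important difference and its SD are not stated. Solving the noncentral t for 80% power at 14.4 per arm gives d = 1.083, used below.

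**Time-by-group test.** Under compound symmetry the noncentrality is

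lambda = (n/2) × SS / (1 − rho),

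where SS is the sum of squares of the arm differences at T1 to T4 about their own mean, with 3 and 3(2n − 2) degrees of freedom.

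- T2 only, (0, d, 0, 0): mean d/4, SS = (3/4)²d² + 3 × (1/4)²d² = 0.75d².
- Lasting, (0, d, d, d): mean 3d/4, SS = (3/4)²d² + 3 × (1/4)²d² = 0.75d².

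The two are identical. With n = 14.4 and d = 1.083:

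| rho | lambda | power, T2-only effect | power, lasting effect |
|---|---|---|---|
| 0.3 | 9.06 | 69% | 69% |
| 0.5 | 12.68 | 84% | 84% |
| 0.7 | 21.13 | 98% | 98% |

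**Group effect.** The average arm difference is d/4 for the T2-only profile and 3d/4 for the lasting one, so this test does distinguish them. Simulated with 14 per arm over the same correlations, it is significant in about 13–17% of trials for T2-only and 65–85% for lasting. It remains an average over visits and does not identify T3 or T4.

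**Other correlation structures.** The equality is special to compound symmetry. With first-order autoregressive correlation 0.7, 14 per arm and d = 0.8, the time-by-group test is passed by T2-only against lasting in 56% against 52% of trials (Greenhouse-Geisser) and 81% against 57% (multivariate). In most settings run, the vanishing effect passes more often.

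**Visit-specific contrasts.** The proportion of simulated trials in which T2, T3 and T4 are all significant (14 per arm, d = 1.083, compound symmetry) is:

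| rho | lasting, T1 as covariate | lasting, change from T1 with pooled ANOVA error |
|---|---|---|
| 0.3 | 57% | 42% |
| 0.5 | 71% | 63% |
| 0.7 | 91% | 89% |

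A T2-only effect passes all three in under 1% of trials with either method.

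**The case against.** The strongest reply is that the article sets no trap. The Discussion sentence is a belief, not a success criterion, and nothing says that a significant interaction alone will be read as an effect at every visit. Follow-up contrasts are routine after such an ANOVA and may stand in a full protocol or SAP that is not shown. This stands: a reader might infer that a false durability claim is built into the plan, and the article does not support that inference. What remains is a mismatch within the article itself, between the question it poses about T3 and T4 and the tests it names to answer it.

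A second reply is that the plan is more than its interaction term. That is also right. The group effect favours a lasting profile clearly, so it would be wrong to say that the plan as a whole treats fading and lasting effects alike. It still cannot say at which visits the arms differ.

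A third reply is that equal power depends on compound symmetry and equal d. It does, and the article supports neither assumption. A reader might take the equality as general, and it is not. Relaxing compound symmetry does not rescue the test, however, because the fading effect then usually passes more often.

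Finally, one could read the Discussion as predicting an effect at T1 too. Since T1 is labelled pre-intervention and randomisation follows it, this is loose wording and no part of the point.

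**Conclusion.** The point holds in a limited form. The article announces a question about stability and an expectation at each assessment, and the tests it names do not by themselves answer either. A significant time-by-group effect is equally likely under a T2-only and a lasting effect (about 69%, 84% and 98% at rho 0.3, 0.5 and 0.7) when d is equal, compound symmetry holds, d is 1.08 and 14.4 per arm are analysed. The group effect helps partly but does not establish an effect at T3 or T4. The values of d and rho are assumptions, and the power figures move with them. The logical gap does not depend on them. The trial's validity is not in question. This is a change worth making to the analysis section, not evidence that a wrong conclusion will be drawn.

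**What to change.** In the Data analysis section, for the COPM, state that the F-CaST minus standard care difference will be estimated at T2, T3 and T4 with 95% CIs, with the T1 score as a covariate. Test in the fixed order T2, T3, T4, each at 0.05, and stop at the first non-significant result. Claim a lasting effect only as far as the sequence succeeds, and report the omnibus time-by-group test as supportive. Reword the Discussion expectation to refer to the three post-intervention assessments.

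The fixed order controls error over visits within the COPM only. It does nothing for multiplicity across outcomes.

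The cost is a few lines of text and a harder claim: under the assumptions above, a true lasting effect reaches significance at all three visits in about 57%, 71% or 91% of trials. If change-from-T1 contrasts from the ANOVA were used instead, this would fall to about 42%, 63% or 89%, which is the reason to prefer covariate adjustment. The T2 test comes first at the full 0.05, so it loses nothing to the later ones.

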## Data Availability

Study data will be made available from the corresponding author upon reasonable request.
